**Methods:**

The study is an open-label, single-center, randomized controlled trial and aims to recruit 456 patients, with 228 patients in each group. The primary outcome was CV; the second outcomes measures are occurrence of bleeding events, ischemic events, heparin-induced thrombocytopenia, deep vein thrombosis, cerebral venous circulation time, brain edema score, and hydrocephalus incidence.

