## Methods

### Study design

This is a prospective, single-center, double-blind, randomized controlled trial. The protocol has been approved by the Ethics Committee of Shenzhen Baoan People’s Hospital (BYL20220805) and registered on ClinicalTrials.gov (NCT05696639). The trial will be conducted at a tertiary teaching hospital in Shenzhen, Guangdong Province, China (Shenzhen Baoan People’s Hospital). This hospital covers an area of approximately 40,000 square meters and has more than 1000 beds, serving a population of approximately 580,000 million residents (data revised in 2020), and the study protocol follows the SPIRIT checklist. The schedule for participant enrollment, intervention, and assessment is based on the SPIRIT figure (Fig. 1).

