### Study intervention

#### Randomization and blinding

This is a randomized, double-blind, controlled trial in which participants will be randomly assigned to one of two groups: the UFH group and the LMWH group. Participants will be unaware of their treatment assignment. The study aims to recruit 286 patients, with 143 patients in each group. Randomization will be conducted using a randomization sequence generated by R software. The specific method for randomization is as follows: install and load the rlist package, generate participant IDs, and use the shuffle function to randomize the participant IDs. The randomized ID data will then be arranged in order, with IDs 1–143 assigned to the UFH group and IDs 144–286 assigned to the LMWH group. Randomization will be performed by an assistant who is not involved in the study, and detailed information regarding the allocation will be kept in sealed envelopes labeled with a sequence number and will not be disclosed to participants. Data evaluation and analysis will be conducted by independent researchers under the supervision of an independent statistician. Participants, data-collecting researchers, and follow-up teams are precluded from making group allocations.

Severe adverse events include shock caused by thrombocytopenia and cerebral hemorrhage. If a severe adverse event occurs, the intervention should be discontinued if necessary, and the patient should receive appropriate rescue treatment. Blinding will be opened, and the event will be reported to the institutional review board. Compensation will be provided to subjects who are injured as a result of participating in the trial. Medical data will still be collected and analyzed. If a general adverse event occurs, patients do not need to be unblinded.

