### Interventions, administration and duration

As part of the trial design, all enrolled patients will receive intervention following embolization of the aneurysm. The UFH group will start intravenous infusion of UFH 24 h after the embolization procedure, upon confirmation of inactive bleeding through head CT scan. The heparin will be administered at a dose of 8–10 U/kg/h, and APTT values will be monitored twice a day for 7 consecutive days. The infusion rate of heparin will be adjusted based on APTT values to maintain it within the range of 35–45 s. In case of APTT values exceeding or falling below the set range, the infusion rate will be decreased or increased by 1 IU and maintained for 12 h. As per FDA standards for the use of low molecular weight heparin, the UFH group will receive subcutaneous injection of prophylactic dose of LMWH (4000 IU) every 12 h for a duration of 1 week starting 24 h after the aneurysm repair.

All experimental UFH is stored in original packaging at 15–30 °C (protected from light and heat). LMWH is stored at 2–8 °C. After opening for more than 24 h, heparin should be discarded. During the administration process, the nursing staff is trained on medication usage and provided with dosing instructions and adverse reaction management plans for both the UFH and LMWH group. To ensure blinding, any communication between the research staff and participants that may reveal group allocation should be avoided. The identity of the medication provider should also not be disclosed.

During hospitalization, both groups of patients will be closely monitored for vital signs and symptoms in the intensive care unit. Platelet-inhibiting agents, nonsteroidal anti-inflammatory drugs, and oral anticoagulants are prohibited during the patient’s treatment period. Physicians will check for interactions with heparin when using other medications and closely monitor bleeding symptoms, adjusting the dosage of heparin or other medications as needed. All patients will receive oral nimodipine, and the blood volume will be maintained in equilibrium. The intracranial pressure of all patients will be monitored with the transducer. Transcranial Doppler (TCD) ultrasound will be performed daily to evaluate for CV, and a weekly follow-up head CT will be performed. In cases where CV or increased intracranial pressure is suspected, urgent head CT angiogram (CTA) or CT scans will be performed for confirmation.

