### Primary and secondary outcomes

The primary outcome was the incidence of CV, while secondary outcomes included the incidence of bleeding events, ischemic events, HIT, deep vein thrombosis, cerebral venous circulation time, brain edema score, and incidence of hydrocephalus. The time points for the primary outcomes are the first and second weeks following the patient’s hospitalization and intervention treatment. The time points.for the secondary outcomes include the first 3 days after hospitalization, the first and second weeks, and the follow-up within 1 year after discharge. The CV was defined as the presence of significant neurological deficits in patients, with TCD ultrasound assess a mean flow velocity of the middle cerebral artery (MCA) exceeding 120 cm/s or a Lindegaard ratio (mean flow velocity of MCA/mean flow velocity of extracranial internal carotid artery) greater than 6. Computed tomography angiography scans showed temporary narrowing of cerebral artery. Regardless of the severity or clinical status of the patient, it was evaluated as CV.

Bleeding events are defined as bleeding that occurs in any part of the body, including intracerebral hemorrhage, gastrointestinal bleeding, and subcutaneous bleeding. According to the standardized bleeding score of Bleeding Academic Research Consortium (BARC), it has 5 types [18]. Type 1 refers to bleeding that is considered insignificant and does not prompt the patient to seek medical attention. Type 2 bleeding includes any obvious sign of hemorrhage that requires medical attention, diagnostic testing, hospitalization, or treatment by a healthcare professional. Type 3 bleeding encompasses clinical, laboratory, and/or imaging evidence of bleeding that requires a specific response from a healthcare provider. Type 4 bleeding is related to coronary artery bypass grafting within 48 h, and type 5 bleeding is fatal. Fatal bleeding can be categorized as intracranial, gastrointestinal, retroperitoneal, pulmonary, pericardial, genitourinary, or other.

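### CTA narrowing is part of the primary outcome, but CTA is prompted by undefined suspicion among staff who may know the arm, so recorded CV could differ between arms without a true difference

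*Protocol article*

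**What the plan says.** **Imaging.** Under Interventions, administration and duration, every patient is screened: "Transcranial Doppler (TCD) ultrasound will be performed daily to evaluate for CV". Arterial imaging is conditional: "In cases where CV or increased intracranial pressure is suspected, urgent head CT angiogram (CTA) or CT scans will be performed for confirmation". This section links suspicion to no TCD value, deficit score or named decision-maker.

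**Outcome.** Under Primary and secondary outcomes, CV is defined by significant neurological deficits together with a TCD finding, namely "mean flow velocity of the middle cerebral artery (MCA) exceeding 120 cm/s or a Lindegaard ratio" above 6. Two separate sentences follow: "Computed tomography angiography scans showed temporary narrowing of cerebral artery" and "Regardless of the severity or clinical status of the patient, it was evaluated as CV". The text does not say whether narrowing on CTA is required in addition to deficit and TCD, is sufficient alone, or merely supports them.

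**Blinding.** The abstract says "The study is an open-label, single-center, randomized controlled trial". Study design says "This is a prospective, single-center, double-blind, randomized controlled trial", and Randomization and blinding also says double-blind, but the only people it describes as unaware of the assignment are the patients: "Participants will be unaware of their treatment assignment". The UFH arm has a continuous infusion adjusted to twice-daily APTT. No dummy infusion is described for the other arm.

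**The concern.** A CTA finding can enter the primary outcome only for a patient who has had a CTA. If the decision to scan rests on bedside judgement made after randomisation, and those judging may know the arm, the chance that a true case is verified can differ by arm. This is differential verification, and it is a separate matter from who reads the images: a blinded reader cannot classify a scan that was never done.

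The problem arises on both main readings of the definition. If CTA narrowing is required, true cases that are not scanned are not counted. If narrowing alone is enough, the arm scanned more often yields more recorded CV. The direction is not fixed. Fewer scans under UFH would produce a spurious benefit, and more scans would hide a real one.

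**Working it through.** **1. Can arm-dependent verification occur if the plan is followed as written?** It needs three conditions.
- *CTA contributes to the outcome.* The definition has a sentence on CTA narrowing, and the imaging rule gives confirmation as its purpose. The condition would fail only if deficit plus TCD settled every case and CTA added nothing; neither sentence supports that.
- *CTA is selective.* It is prompted by suspicion of CV or of raised intracranial pressure, with no criterion.
- *Those who select may know the arm.* Treating staff are not stated to be blinded, nurses receive dosing instructions for both groups, and the infusion is visible.

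All three hold on the text shown.

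**2. Inputs for an illustration of size.**
- True CV: 60% in both arms. This is the LMWH figure under Sample size estimation, applied equally so that the null hypothesis is true.
- Evaluable patients: 228 × 0.9 = 205 per arm (Sample size estimation, 10% dropout). Randomization and blinding instead gives 143 per arm: 143 × 0.9 = 128.7, taken as 128. Both are shown because the article does not settle which applies. The derivation of 228 is a separate matter and does not affect this point.
- Test: two-sided, α = 0.05.
- Share of true cases imaged in each arm: **assumed**, since the document gives none.
- Reading of the definition: CTA **required**.

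**3. Formulae.** Recorded rate in an arm: p = 0.60 × share imaged. For the pooled two-proportion z-test with n per arm, write d = p₁ − p₂ and p̄ = (p₁ + p₂)/2. Then

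s₀ = √[2p̄(1 − p̄)/n], s₁ = √[(p₁(1 − p₁) + p₂(1 − p₂))/n],

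P(reject) = Φ[(d − 1.96 s₀)/s₁] + Φ[(−d − 1.96 s₀)/s₁].

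**4. Worked case: 95% v 85%, n = 205.** p₁ = 0.60 × 0.95 = 0.57 and p₂ = 0.60 × 0.85 = 0.51, so d = 0.06 and p̄ = 0.54. s₀ = 0.0492 and s₁ = 0.0491. The first term is Φ(−0.742) = 0.229; the second, Φ(−3.185), is below 0.001. P(reject) = 0.23.

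**5. Results.**

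| Share of true cases imaged | Recorded CV | False difference | False positives, n = 205 | False positives, n = 128 |
|---|---|---|---|---|
| 90% v 90% | 54% v 54% | 0 points | 5% | 5% |
| 95% v 90% | 57% v 54% | 3 points | 9% | 8% |
| 95% v 85% | 57% v 51% | 6 points | 23% | 16% |

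The first row shows that incomplete imaging that is equal between arms creates no false difference; only a gap between arms does. If the target effect of 0.1 under Sample size estimation means 10 percentage points, a 6-point artefact is 60% of it.

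**6. Sensitivity to the true rate.** With true CV of 40% and the 95% v 85% gap, recorded CV is 38% v 34% and the false-positive rate is about 13% at n = 205.

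**The case against.** Several counter-arguments have force.

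- *TCD probably feeds suspicion already.* The daily TCD sentence comes just before the imaging rule, and the natural reading is that a raised velocity prompts a scan. A reader might infer that the plan sets TCD aside in favour of clinical impression; the text does not say that. It states no link either, so discretion remains.
- *Suspicion of CV may not be the only route to CTA.* Raised intracranial pressure is a second trigger, and pressure is monitored in all patients. The PRECISE score, part of a secondary outcome, is read from head CTA, and the first- and second-week time points are shared with the primary outcome. Some CTA may therefore be scheduled in Table 1, which is not shown. That would shrink the problem, but suspicion-led scans on top could still be unequal.
- *Plain CT as confirmation of CV.* A reader might infer that the protocol accepts it. The wording can equally pair CTA with CV and CT with raised pressure, so this is an ambiguity and not an error.
- *Blinding is claimed.* Study design and Randomization and blinding say double-blind, Recruitment says allocation stays confidential, and independent researchers evaluate the data. These statements conflict with the abstract, do not name treating staff as blinded, and cannot govern which scans are done.
- *The figures rest on assumed gaps.* This is correct. If deficit, TCD and CTA are all required, a missed case would have a significant deficit and a raised velocity yet arouse no suspicion, so large gaps are implausible. If CTA alone suffices, the calculation does not apply. A reader might take 23% as an expected error rate; the documents give no basis for that.
- *The bias cannot be dealt with in analysis.* That would be too strong. Scans never done cannot be recovered, but TCD measured daily in everyone allows a sensitivity analysis that can partly expose the bias.

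What stands is that the stated trigger is discretionary, it bears on the sole primary outcome, and those using it may know the arm.

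**Conclusion.** The concern holds in a limited form. As written, the plan permits verification of CV to depend on the arm, because an undefined suspicion governs access to a test that is part of the primary outcome, the combination rule is unstated, and blinding of treating staff is not established. It does not show that such bias will occur, or in which direction.

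The illustrated size, a false-positive rate of about 9% to 23% with 205 per arm or 8% to 16% with 128, rests on equal true CV of 60%, CTA being required, and imaging gaps of 5 to 10 points that are assumptions. It shows how sensitive the result is to modest gaps and is not a prediction. Scheduled CTA or a TCD-led practice would bring the rates closer to 5%. The point merits a change before recruitment because the protocol already collects an objective daily measure in every patient that can be used for this purpose.

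**What to change.** Reconcile Interventions, administration and duration with Primary and secondary outcomes, **for outcome classification only**. Clinical ordering of imaging is left unchanged.

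1. Prespecify one arm-independent criterion for CV based on the protocol's own daily TCD limits (MCA mean velocity above 120 cm/s or Lindegaard ratio above 6), and state how TCD, deficit and CTA combine.
2. State that plain CT does not establish arterial narrowing for the primary outcome.
3. Keep all clinically ordered CTAs and have them classified by assessors blinded to arm.
4. Add a sensitivity analysis of the primary outcome using the TCD criterion, which is measured in every patient.
5. Report by arm the number of patients crossing a TCD limit and the number of CTAs done.

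**Cost.** Protocol wording, blinded classification of scans already taken, and a little more analysis. TCD is already daily, so the change adds no patient measurement. The drawback is that the TCD-based rate may differ from the CTA-confirmed rate, and the report would have to explain any gap.

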### Intervention discontinuation

Throughout the entire period of the trial, we will establish a data and safety monitoring committee (DSMC) to oversee the progress of the clinical trial, establish an adverse event reporting system to record and report any serious adverse events (SAE) or unexpected outcomes, establish an emergency unblinding procedure to address any serious medical issues that may arise during the trial, develop contingency plans to address any unexpected interruptions or delays that may affect the trial process, and take measures to minimize the impact of any possible interruptions. The researchers do not have the right to decide on the withdrawal of participants, and all discontinuation and deviations from the study protocol will be recorded and reported to the DSMC, regulatory agencies, and the study sponsor.

### Confidentiality

All medical data and personal information of the participants will be kept confidential in accordance with international guidelines and regulations. Only designated members of the research team will have access to participant data, and access will be limited to the information necessary to perform their specific duties. Participant identification codes will be used instead of participant names to ensure anonymity and confidentiality. Data sharing and confidentiality agreements will be developed as needed to protect the confidentiality of research data, analytical methods used, and results obtained. Participants’ medical data and personal information will be encrypted, password protected, or stored offline as needed to ensure data security. All documents related to the study, including informed consent forms and participant medical records, will be securely stored in designated locations to ensure confidentiality.

### Outcome assessments

#### Baseline assessment

Baseline variables encompass demographic information (gender, age, ethnicity, prior medical history, personal life history), comorbidities, vital signs (blood pressure, heart rate, respiratory rate), concomitant medication, surgical intervention (e.g., decompressive craniectomy), and results of the laboratory tests. In addition, Hunt-Hess scales [14] and World Federation of Neurosurgery Societies (WFNS) [15] grade were used to assess the severity of clinical symptoms. Modified Fisher score [16] was employed to evaluate the degree of CV. Assessment of functional independence was performed by the Modified Rankin Scale (mRS) [17]. All clinical baseline data were conducted upon admission and during hospitalization by two researchers who were unaware of the group assignment.

### Primary and secondary outcomes

The primary outcome was the incidence of CV, while secondary outcomes included the incidence of bleeding events, ischemic events, HIT, deep vein thrombosis, cerebral venous circulation time, brain edema score, and incidence of hydrocephalus. The time points for the primary outcomes are the first and second weeks following the patient’s hospitalization and intervention treatment. The time points.for the secondary outcomes include the first 3 days after hospitalization, the first and second weeks, and the follow-up within 1 year after discharge. The CV was defined as the presence of significant neurological deficits in patients, with TCD ultrasound assess a mean flow velocity of the middle cerebral artery (MCA) exceeding 120 cm/s or a Lindegaard ratio (mean flow velocity of MCA/mean flow velocity of extracranial internal carotid artery) greater than 6. Computed tomography angiography scans showed temporary narrowing of cerebral artery. Regardless of the severity or clinical status of the patient, it was evaluated as CV.

Bleeding events are defined as bleeding that occurs in any part of the body, including intracerebral hemorrhage, gastrointestinal bleeding, and subcutaneous bleeding. According to the standardized bleeding score of Bleeding Academic Research Consortium (BARC), it has 5 types [18]. Type 1 refers to bleeding that is considered insignificant and does not prompt the patient to seek medical attention. Type 2 bleeding includes any obvious sign of hemorrhage that requires medical attention, diagnostic testing, hospitalization, or treatment by a healthcare professional. Type 3 bleeding encompasses clinical, laboratory, and/or imaging evidence of bleeding that requires a specific response from a healthcare provider. Type 4 bleeding is related to coronary artery bypass grafting within 48 h, and type 5 bleeding is fatal. Fatal bleeding can be categorized as intracranial, gastrointestinal, retroperitoneal, pulmonary, pericardial, genitourinary, or other.

Ischemic events include cerebral and cardiac ischemia, with cerebral ischemia encompassing transient ischemic attacks and stroke, while cardiac ischemia includes angina pectoris and myocardial infarction. HIT is defined as a decrease in platelet count of 50% or more after the therapy of heparin. Deep venous thrombosis includes lower limb deep venous thrombosis and pulmonary embolism, which is diagnosed by a respiratory physician based on pulmonary vascular examination and blood D-dimer testing. The diagnose of lower limb deep venous thrombosis is detected by ultrasound. Hydrocephalus is defined as an enlargement of the cerebral ventricles as visualized on a brain CT scan.

Cerebral venous circulation time is defined as the time required for blood to enter the venous sinus through the deep and superficial veins of the brain and then be drained into the jugular vein, including microvascular cerebral circulation time, venous cerebral circulation time, and the PRECISE score. Following S. Wang’s research, the starting point T1 is set as the first image in the sagittal view of digital subtraction angiography (DSA), which depicts the contrast dye within the branches of the middle cerebral cortical arteries [19]. The vein image that shows the peak filling of the parietal cortical vein is set as T2, and the only disappearance of the sigmoid sinus was set as T3. The mCCT is expressed as T2-T1, while vCCT is expressed as T3-T2.

The PRECISE score is based on the venous filling level shown on the head CTA. A score of 2 represents complete filling that is consistent with the degree of filling in the contralateral hemisphere, while a score of 1 represents partial filling, and a score of 0 indicates no filling. The filling difference of the affected hemisphere veins is calculated based on the PRECISE score. A higher score indicates the improved cerebral venous outflow, while a lower score signifies the decreased cerebral venous outflow. A score of 2 will be given for “complete” contrast filling of the opposite hemisphere, while a score of 1 will be given for “partial” (moderate contrast filling). The PRECISE score will be calculated using the composite score of the normal hemisphere SMCV + VOT + VOL + BVR minus the composite score of the lesioned hemisphere SMCV + VOT + VOL + BVR [20].

The assessment of brain edema is mainly based on SEBES score which is mainly based on head CT images and intracranial pressure monitoring values during hospitalization [21]. Head CT scans will be conducted at four stages: at the time of admission (0–2 days after aSAH), after endovascular treatment (4–7 days after aSAH), during hospitalization (7–14 days after aSAH), and before discharge (14–21 days after aSAH). Two blinded neurologists specializing in cerebrovascular diseases will independently evaluate the SEBES value of the patients. The scoring criteria will range from 0 to 4 points. Two pre-determined levels in each hemisphere will be defined, and 1 point will be given for visible sulcal effacement due to the interruption of the gray-white matter connection. Intracranial pressure monitoring will include intracranial ICP monitoring, which is recorded by placing an intracranial probe.

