In patients undergoing endovascular treatment for aSAH, continuous maintenance of arterial catheters with UFH during surgery contributes to the reduction of thrombus formation, while subcutaneous injections of low-molecular-weight heparin (LMWH) prevent formation of lower-extremity deep veinous thrombosis. However, both LMWH and UFH infusions have their pros and cons. Although neurocritical care guidelines recommend initiating subcutaneous heparin 24 h after aneurysm embolization surgery [9], the UFH injection has limitations due to its high molecular weight and low bioavailability. Intravenous UFH may, therefore, be considered more reliable.

Research indicates that low-dose intravenous UFH infusion yields favorable outcomes in reducing CV and ischemic complications. Multiple retrospective studies have demonstrated the safety and efficacy of low-dose continuous intravenous UFH infusion. However, there is controversy regarding the optimal dosage and duration of treatment. A retrospective study by J. Marc Simard revealed the safety of low-dose (8–9 U/kg/h) intravenous UFH administration in aSAH patients, without any cases of bleeding, heparin-induced thrombocytopenia (HIT), or deep vein thrombosis, and the incidence of clinical vasospasm significantly decreased compared to subcutaneous LMWH usage [10]. Another research by Markus Bruder in endovascular treatment for aSAH patients showed a lower probability of cerebral infarction when combining UFH with LMWH [11].

Regarding the timing of initiating of heparin, Annika’s study suggested that using heparin within 24 h after aneurysm repair might be safer and carry a lower risk of bleeding compared to initiating treatment 48 h later [12]. Randomized controlled trial results comparing subcutaneous injections of LMWH and intravenous infusion of UFH are currently lacking, although randomized controlled studies have shown the safe and effective reduction of CV and ischemia with subcutaneous injection of enoxaparin compared to placebo in patients with aSAH [13].

This study is a single-center exploratory randomized controlled trial comparing the impact of low-dose intravenous infusion of UFH and subcutaneous injection of LMWH on the incidence of CV in aSAH patients. The outcomes to be assessed also include the occurrence of bleeding events, ischemic events, HIT, deep vein thrombosis, cerebral venous circulation time, brain edema score, and hydrocephalus incidence.

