### Sample size estimation

The primary outcome of this study was the incidence of CV. J. Marc’s research indicated that the incidence of CV was 58% and 60% in the groups receiving intravenous unfractionated heparin and subcutaneous low molecular weight heparin, respectively [10]. The hypothesis was that the unfractionated heparin protocol was superior to the subcutaneous low molecular weight heparin injection in reducing the incidence of CV. The sample size of the study was calculated using a bilateral test to achieve a target effect of 0.1 and an α error of 0.05. Considering a dropout rate of 10%, each group would require 228 patients, so a total of 456 participants will be enrolled. The sample size was estimated using PASS (version 15.0.3, NCSS, LLC, Kaysville, Utah, USA).

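### The primary outcome definition contradicts itself on whether a neurological deficit is required, so the same patients can give different primary results

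*Protocol article*

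**What the plan says.** All of the following is in the Protocol article.

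- **Endpoint.** Primary and secondary outcomes: "The primary outcome was the incidence of CV, while secondary outcomes included the incidence of bleeding events".
- **Opening of the definition.** "The CV was defined as the presence of significant neurological deficits in patients, with TCD ultrasound assess a mean flow velocity", with the TCD limits on the middle cerebral artery (MCA) given as "exceeding 120 cm/s or a Lindegaard ratio" above 6. As worded, the deficit and the TCD finding are both needed.
- **CTA.** The next sentence reads "Computed tomography angiography scans showed temporary narrowing of cerebral artery". No conjunction shows whether this is required, is an alternative, or confirms.
- **Close of the definition.** "Regardless of the severity or clinical status of the patient, it was evaluated as CV".
- **Timing.** "The time points for the primary outcomes are the first and second weeks following" hospitalization and intervention treatment. The article does not say whether this is one cumulative period or two readings.
- **How the data arise.** Under Interventions, administration and duration, TCD is daily in all patients. CTA or CT is done only when CV or raised intracranial pressure is suspected, as confirmation.
- **Planning rates.** Sample size estimation, citing reference 10: "the incidence of CV was 58% and 60% in the groups receiving intravenous unfractionated heparin and subcutaneous low molecular weight heparin".
- **The same reference in the Background.** "the incidence of clinical vasospasm significantly decreased compared to subcutaneous LMWH usage".

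**The concern.** Whether a deficit is required separates two recognised endpoints: symptomatic vasospasm and vasospasm seen on a test. The article's definition contains both and does not choose. This is more than detail left to a fuller document, because the rule is given and its parts conflict.

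Three things are at stake. Two competent analysts could report different primary results from the same data. The choice could be made, even innocently, after results are known. The event rate used to size the trial may belong to a different endpoint from the one finally analysed.

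The article's own account of reference 10 suggests that the choice matters: it reports a significant reduction in clinical vasospasm in one place and CV rates two points apart in another.

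**Working it through.** **1. Four possible readings, applied to the same patients.**

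A = deficit and TCD. B = TCD or CTA, any clinical status. C = (deficit and TCD), or CTA narrowing at any status. D = TCD confirmed by CTA, any status.

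| Patient | A | B | C | D |
|---|---|---|---|---|
| MCA 130 cm/s, no deficit, no CTA done | no | yes | no | no |
| MCA 130 cm/s, no deficit, CTA narrowing | no | yes | yes | yes |
| MCA 130 cm/s, deficit, CTA clear | yes | yes | yes | no |
| TCD below limits, no deficit, CTA (done for raised pressure) shows narrowing | no | yes | yes | no |

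Every row is classified differently by at least two readings. The text does not exclude any of the four.

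**2. Can the choice change the result?** The planned 228 per group less 10% dropout leaves 228 × 0.9 ≈ 205 per arm. Patients with a deficit and a TCD finding are a subset of those with the finding at any status. The counts below are assumed, because the article gives none for the deficit-required endpoint. The any-status proportions are set close to the planning rates. The test is the Pearson chi-square without continuity correction, z = (p1 − p2)/√[p̄(1 − p̄)(2/205)].

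- Deficit required: UFH 41/205 (20.0%), LMWH 62/205 (30.2%). p̄ = 103/410 = 0.251, SE = 0.0428, z = −2.39, p = 0.017.
- Any status: UFH 119/205 (58.0%), LMWH 123/205 (60.0%). p̄ = 242/410 = 0.590, SE = 0.0486, z = −0.40, p = 0.69.

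The counts are compatible: the deficit-free cases are 119 − 41 = 78 and 123 − 62 = 61. One reading is significant and the other null.

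**3. What happens to power?** The plan's own 228 per group does not reproduce from the inputs it states. At an assumed 80% power, two-sided 0.05, 60% v 50% needs 388 per arm (432 with 10% dropout). That is a separate matter, so 205 per arm is taken as given. Power = Φ{[|d| − 1.96√(2p̄(1 − p̄)/n)] / √[(p1(1 − p1) + p2(1 − p2))/n]}. The symptomatic rates of 20% and 30% are assumptions.

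| Control rate | Same relative reduction (one sixth) | Same absolute reduction (0.10) |
|---|---|---|
| 60% | 60 v 50: 53% | 60 v 50: 53% |
| 30% | 30 v 25: about 20% | 30 v 20: 65% |
| 20% | 20 v 16.7: about 14% | 20 v 10: 81% |

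If the endpoint is rarer, power falls with the relative effect fixed and rises with the absolute effect fixed. The article states a target effect of 0.1. Read as absolute, that corresponds to the right-hand column.

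**4. The window (lesser point).** If, and only if, weeks 1 and 2 were each tested at 0.05, the familywise error would be 1 − 0.95² = 9.75% for independent tests. For nested cumulative counts it would be about 7.7% to 9.3%, assuming 50% to 20% CV by week 1 and 60% by week 2.

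On the clock, admission may be up to 72 h after onset and heparin starts 24 h after embolization. The first dose can therefore fall on about day 4 or later, while the Background puts CV typically at days 3–14. Some CV can precede treatment. Fourteen days from a day-4 dose is day 18, and the pre-discharge CT is placed at 14–21 days after aSAH. A window counted that way could outlast the daily TCD.

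**The case against.** The strongest defence is reading C over one two-week period: the clinical-status sentence follows the CTA sentence and may apply only to it. That is coherent, but the article does not say it. It would also make case-finding by CTA depend on who is suspected of CV, in a trial called open-label in the abstract and double-blind in the Methods. The contradiction stands.

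Several stronger inferences are tempting, and the documents do not support them.

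- **That the readings would give opposite results.** A full reversal can be constructed: 41 v 62 with a deficit, but 133 v 113 at any status, p = 0.044 favouring LMWH. It needs contrived counts. Significant against null is the likelier form.
- **That a deficit-required endpoint would cut power to 14–20%.** This holds only if the relative effect is fixed. On the absolute scale power rises to 65–81%.
- **That reference 10 proves the choice decides the answer.** The article does not say what kind of CV the 58% and 60% measure. The two sentences may simply describe the source inconsistently.
- **That type I error is inflated.** The two weeks may mean one period, separate testing is not stated, and multiplicity can be left to an analysis plan.
- **That pre-treatment CV biases the comparison.** Under randomisation it would mainly dilute the effect, and its share is unknown.
- **That assessors will choose the definition to suit the result.** The article provides for independent evaluation under an independent statistician. The ambiguity leaves room for a late choice but does not show that one is intended.

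**Conclusion.** The concern holds for the definition. The primary outcome is wrong as written, because a patient above the TCD limits without a deficit is both a non-case and a case, and the place of CTA is undefined. This should be settled before any outcome data are examined by arm.

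Its size can only be illustrated. Under the assumed counts the primary p-value is 0.017 on one reading and 0.69 on the other. The article's two descriptions of reference 10 are consistent with such a split but do not establish it. The 60% planning rate carries no deficit qualifier and may not fit a deficit-required endpoint. A definite loss of power is not shown.

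The unstated window and clock are a lesser point, to be cleared up in the same edit.

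**What to change.** 1. **One rule with explicit logic.** Primary CV = MCA mean velocity above 120 cm/s or Lindegaard ratio above 6 on the daily TCD done in all patients, irrespective of neurological status. This follows the closing sentence of the definition and rests on a measurement made in everyone.
2. **CTA.** State whether narrowing on CTA confirms a TCD case or adds one. Because CTA is obtained only on suspicion, any route by which it adds cases should be acknowledged as depending on suspicion.
3. **Symptomatic CV.** Make it a secondary outcome: the same criterion plus a new neurological deficit.
4. **Window.** State that the primary analysis is any CV through the second week, as one cumulative count from one stated start point, within the period when daily TCD is done. Report week 1 descriptively.
5. **CV before the first dose.** Record it, and state whether those patients stay in the denominator and whether they can still become cases.
6. **Planning rate.** Confirm that the 60% refers to the chosen definition, and revisit the sample size if it does not.

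**Cost.** Items 1 to 5 are mainly wording, since daily TCD is already planned; item 5 also needs a recorded data item. A separate week-1 claim is given up. Item 6 requires going back to the source and may change the sample size justification.
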